### Sample size

A pilot study was conducted in August 2016 with 100 women who were already part of the WfWI intervention to assess the questionnaire, as well as provide an estimate of physical IPV experience in the past 12 months. We found many of the women already enrolled in the WfWI intervention were not currently married, in fact only 37/100 were. Among these, past year physical IPV prevalence was 32.4% and past year severe IPV prevalence was 27%. At the time, this corresponded to published data, which estimated 39.3% of women had experienced past year physical IPV [16].

We used an assumption of seeing an effect size of 0.3 difference between the 12 month prevalence of physical IPV at endline in the control and intervention arms. This is the effect size seen in several recent evaluations of effective violence prevention interventions [18, 19]. We assume that the 12 month control arm IPV prevalence will be 32% and severe IPV 27%. Using Stata, with power set at .80 and alpha at 0.05, sample size per arm was estimated to be 337 for past year physical IPV, and 422 for past year severe physical IPV. Based on our calculations for the percentage of women recruited into the intervention being currently married, and the potential loss to follow-up, the target number of participants was 1477.

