### Outcomes

While traditional evaluations of interventions define one primary outcome, complex interventions, such as this, have increasingly defined multiple primary outcomes that are equally important [19–21]. The primary and secondary outcomes are detailed in Table 1 with questionnaire items used to evaluate outcomes, an example per outcome, and hypothesized direction of change. The trial has three primary outcomes:Past year experience of physical IPV amongst currently married womenPast year experience of severe physical IPV amongst currently married womenWomen’s past week depressive symptoms

**Table 1 Tab1:** Primary and secondary outcomes for the trial

	Number of items and origins	Example question and response categories	Scaling	Alpha	Hypothesized direction
Primary outcomes					
Past year experience of physical IPV amongst currently married women	Five items ask about married women’s experience of physical IPV. The scale is based on the WHO’s multi-country study of IPV [25].	(Q) In the past 12 months how many times has your husband hit you with a fist or with something else which could hurt you? (A) Never, once, few, many	A positive response to one or more items coded as yes		Decrease
Past year experience of severe physical IPV amongst currently married women	Same scale as above. Severe physical IPV is defined as experiencing more than one item of the five, or experiencing any one item more than once, creating a dichotomous measure equivalent to more than once experiencing physical IPV.	(Q) In the past 12 months how many times has your husband slapped you or thrown something at you which could hurt you? (A) Never, once, few, many	Two or more items responded to as ‘once’ or responding to any single item as “few”, or “many”.		Decrease
Women’s past week depressive symptoms	Depressive symptoms are assessed using the Center for Epidemiological Studies Depression scale (CES-D), comprising 20 items asking about depressive symptoms in the past week [26].	(Q) During the past week I had crying spells (A) Rarely or none of the time; some or little of the time; moderate amount of time; most or all of the time	Mean score created; higher mean’s more depressive symptoms	0.90	Decrease
Secondary outcomes					

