### Data management and analysis

Questionnaires were double-entered into SPSS, discrepancies between the entered data were identified, and answers were verified through checking the paper questionnaires and corrected. The same process will be undertaken for both follow ups.

The data will be cleaned by the study statistician. One dataset will be compiled for analysis of key variables based on the three data collections: baseline, follow up at the end of the programme (12 months from baseline), and follow up 12 months after programme graduation (24 months from baseline). The data will be described by presenting frequencies for categorical variables and means for scale and sub-scales, with 95% confidence intervals by study arm.

The main analysis for outcomes of intimate partner violence will be conducted on a sub-set of the sample who are currently married at endline. For depression, it will be conducted on the entire sample. Intention-to-treat (ITT) analyses will be conducted. A *per protocol* analysis will also be conducted as a secondary analysis (i.e. including just those women who attended more than 75% of WfWI’s core programme). Cross tabulation and chi-square tests will be used to determine whether there are differences in demographics between the treatment and control group. The primary analysis will be carried out by fitting Generalized Linear Mixed Models (GLMMs) with a term for treatment arm [23]. For outcomes using scales, the difference in the scores between baseline and 12 months, and baseline and 24 months will be assessed. For each of the scales, a linear mixed model will be fitted with fixed terms for treatment arm. The scores will be directly calculated from the component items, while the scales will combine the items using weights determined by carrying out a principal component analysis on the items at baseline, and using the loadings for the first principal component as the weight for each item. These analyses will firstly be carried out on the ITT population and then repeated for the per protocol population.

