## Discussion

### Implementation

In total, six villages in five districts across two provinces were identified and agreed to participate in the study. A seventh village was approached but declined to be part of the study due to the randomisation process. A total of 1461 women were recruited and randomised into the study at baseline. Of the total recruited, 935 were currently married at baseline.

There are some important demographic differences between the districts sampled. In Kalakan district in Kabul, community members are predominantly Tajik with a small proportion of Pashtuns. In Nangarhar province (in both districts), community members are predominantly Pashtun with a small proportion of Tajiks. In Dashte Barchi district of Kabul province, community members are predominantly Hazara.

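### Scale outcomes, including the primary depression score, are planned as change from baseline with only a treatment-arm term named, which is less precise than adjusting for the baseline score already collected

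*Protocol article*

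**What the plan says.** The Data management and analysis section of the protocol article fixes both the quantity and the model for scales. The quantity: "For outcomes using scales, the difference in the scores between baseline and 12 months, and baseline and 24 months will be assessed". The model: "For each of the scales, a linear mixed model will be fitted with fixed terms for treatment arm". The general statement for the primary analysis is similar: "The primary analysis will be carried out by fitting Generalized Linear Mixed Models (GLMMs) with a term for treatment arm". The article names no baseline value as a covariate.

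Depression falls under the scale wording. Table 1 in the Outcomes section lists it as a primary outcome: "Depressive symptoms are assessed using the Center for Epidemiological Studies Depression scale (CES-D), comprising 20 items", scored as a mean. Its analysis set is all women: "For depression, it will be conducted on the entire sample". The secondary outcomes scored as means of several items, such as food insecurity, life satisfaction and gender attitudes, come under the same sentence.

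The baseline scores will be to hand, because the rounds are merged: "One dataset will be compiled for analysis of key variables based on the three data collections: baseline, follow up at the end of the programme".

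**The concern.** A change score subtracts the whole baseline value, as if each point at baseline predicted a full point at follow-up. When the correlation between the two measurements is below 1, that is too much, and baseline noise is carried into the treatment comparison. Regression on baseline subtracts only the part that predicts follow-up.

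At stake are the width of the interval and the power for one primary outcome and the scale secondaries. The protocol's power calculation covers only the two partner-violence outcomes, so nothing in it shows how much precision the depression comparison has to spare.

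**Working it through.** **The plan's own figures.** The Sample size section says: "with power set at .80 and alpha at 0.05, sample size per arm was estimated to be 337 for past year physical IPV", and gives 422 for severe physical violence. With a 30% relative reduction (32% to 22.4%; 27% to 18.9%), two-sided alpha 0.05, power 0.80, equal arms and no continuity correction:

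n per arm = [1.960·√(2p̄(1−p̄)) + 0.842·√(p1(1−p1)+p2(1−p2))]² / (p1−p2)²

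This gives 337 and 422, an exact match. These figures concern the binary outcomes and do not depend on the present point. The article gives no sample size or power for any scale.

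**Inputs for the scale outcomes**
- From the documents: 1461 women randomised (Implementation: "A total of 1461 women were recruited and randomised into the study at baseline"), 747 intervention and 714 control (Limitations).
- Assumed: equal standard deviation S at baseline and follow-up; correlation r from 0.2 to 0.7; for the power illustration, a true difference of 0.15 S. The documents give none of these.

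**Variance of the arm contrast**, relative to using the follow-up score alone (= 1):
- change score: 2(1−r)
- follow-up score adjusted for baseline: 1−r²
- adjusted ÷ change: (1−r²) / [2(1−r)] = (1+r)/2, below 1 for every r below 1
- interval narrowing: 1 − √((1+r)/2)

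**Detectable difference and power.** The standard error factor is √(1/747 + 1/714) = 0.0523. The difference detectable with 80% power is (1.960 + 0.842) × 0.0523 × √V = 0.147√V, in units of S, where V is the relative variance above.

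| r | V, change | V, adjusted | ratio | interval narrower by | detectable difference, change / adjusted | power at 0.15 S, change / adjusted | same with an assumed 20% loss |
|---|---|---|---|---|---|---|---|
| 0.2 | 1.60 | 0.96 | 0.60 | 23% | 0.185 / 0.144 | 62% / 83% | 53% / 74% |
| 0.3 | 1.40 | 0.91 | 0.65 | 19% | 0.173 / 0.140 | 68% / 85% | 58% / 77% |
| 0.5 | 1.00 | 0.75 | 0.75 | 13% | 0.147 / 0.127 | 82% / 91% | 73% / 84% |
| 0.7 | 0.60 | 0.51 | 0.85 | 8% | 0.114 / 0.105 | 96% / 98% | 91% / 95% |

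Below r = 0.5 the change score has a larger variance than ignoring baseline altogether (1.40 against 1 at r = 0.3). Above 0.5 it does better than ignoring baseline, but still worse than adjusting.

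**Where the excess comes from.** 2(1−r) − (1−r²) = (1−r)². If the arms differ by chance by δ at baseline, the change score removes δ where rδ would do, and so misses by (1−r)δ. A chance difference of one standard error (0.0523 S) would shift the estimate by 0.7 × 0.0523 = 0.037 S at r = 0.3, and by 0.3 × 0.0523 = 0.016 S at r = 0.7. The lost precision and the sensitivity to chance imbalance are the same thing, seen on average or for one given allocation.

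**If the mixed model is meant as repeated measures.** With three rounds, an arm-by-visit contrast and no constraint on the baseline means, the estimate in complete data equals the difference in mean change. The loss is the same.

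**The case against.** The strongest reply is that the article names a term for arm but does not say that no other term enters. Covariate lists often sit in an analysis plan, and none is shown here. Nor does assessing a difference exclude adjustment: a change score regressed on arm and baseline gives exactly the same arm effect as the follow-up score regressed on arm and baseline. This stands as a limit: the loss follows if the models are fitted as described, and an unseen covariate list could remove it. It does not displace the point, because the article itself commits to the difference score and to arm terms.

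It is also fair that a change-score comparison is a legitimate analysis of a randomised trial. The depression sample is large, and no CES-D target is stated that the planned analysis would miss. So this is an efficiency gain left unused.

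Three stronger readings are tempting, and the documents do not support them:
- **That the depression result will be biased.** Under sound randomisation the change score is unbiased. Table 2 shows age, relationship status, education and borrowing by arm but no baseline CES-D, so no imbalance in the score is shown.
- **That r is probably low, so the change score is worse than ignoring baseline.** No correlation is given. At r = 0.7 the gain is only about 8% in interval width.
- **That the partner-violence models have the same defect.** The article plans no change score for them, so the absence of a baseline term rests on silence, and the variance formulas are for continuous scores. Their analysis set is women married at endline, while Table 2 counts 428 never married at baseline. Under Eligibility criteria the violence questions were feasible only for women currently or previously married, so baseline status is undefined for anyone who first marries during follow-up.

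**Conclusion.** The point holds for the continuous scale outcomes, including the primary depression score. As described, the analysis has 1/0.60 = 1.67, 1/0.65 = 1.54, 1/0.75 = 1.33 and 1/0.85 = 1.18 times the variance of a baseline-adjusted one at r = 0.2, 0.3, 0.5 and 0.7. The direction is certain for any r below 1 with equal standard deviations; the size depends on an r that the documents do not give. The cost is precision, and sensitivity to a chance difference in the baseline score. It is neither demonstrated bias nor a finding against the binary partner-violence analyses.

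**What to change.** For each scale, state that the 12- and 24-month scores are the outcomes in a linear mixed model with arm, visit, arm-by-visit and the baseline score as covariate. Alternatively, specify a constrained longitudinal model of all three rounds with a common baseline mean. If an analysis plan already lists the baseline score as a covariate, the protocol wording should say so.

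Some scales are asked only of married women, so a woman who marries during follow-up may lack a baseline score. A change score cannot be formed for her either, so the plan needs a rule for such cases under any of these methods.

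For the two partner-violence outcomes, baseline past-year status may be added as an optional covariate, with a separate category for women for whom it was not defined at baseline.

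For the scales, the cost is a change of wording, made before follow-up data are analysed by arm; no new data are needed. The optional violence covariate also needs its extra category defined.

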### Eligibility criteria

The eligibility criteria for the study mostly followed the entry criteria for WfWI. The regular selection criteria for the WfWI intervention were that participants should be at the lowest economic level possible, earning less than a US$1.25 a day, they should be unemployed, not in school and not involved in a similar programme. Women incapacitated due to mental illness or very severe disability would not be eligible for the intervention, as they otherwise would not be able to fully benefit by engaging in the training sessions (e.g. if blind they would be unable to observe the training materials, or if deaf they would be unable to hear the content of the training) or by doing income generating work. Women should be willing to participate in the programme and attend all training classes and not have previously participated in the programme. Preference was given to women who are mothers or heading households, irrespective of marital status. Women were encouraged to secure support from family members for their involvement to better facilitate their participation, although this was not always possible.

Two additional criteria due to the research were added: 1) restricting the age of women to 18 and 45 years due to issues of consent for those under 18 year olds; and 2) increasing the proportion of currently married women in the sample than is general WfWI practice because in Afghanistan, it is only feasible to ask IPV questions of currently married/previously married women. The age restriction also reduced the likelihood of mother-in-laws being recruited into the study alongside their daughter-in-laws. (A pilot study found that having two members of the same household in the study led to concerns about maintaining privacy about the study).

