Married women’s participation in household decision making	Five items are asked about women’s ability to participate in household decisions, based on the WHO Multi-Country Study on Domestic Violence [25].	(Q) In the last three months, how often your views been listened to on matters concerning the children and their schooling or work in your home? (A) Never; sometimes; often	Mean score; higher scores indicate more participation	0.77	Increase
Past year emotional IPV amongst currently married women	Seven items ask about experiences of emotional abuse by the husband.	(Q) In the past 12 months how many times has your husband insulted you or made you feel bad about yourself? (A) Never; once; few; many	Mean score; higher score indicates more emotional violence		Decrease
Perceptions of husband cruelty amongst currently married women	Five items ask about married women’s perceptions of her husband and his attitudes and relationship towards her.	(Q) My husband is very strict and controlling. (A) Strongly disagree; disagree; agree; strongly agree	Mean score: higher scores indicate more cruelty	0.88	Decrease
Mother in law and sibling abuse:	Two items: A single item assesses whether mother-in-laws have hit the woman in the past 12 months and another item assesses whether siblings have hit the woman in the past 12 months, an affirmative response to either item would indicate abuse.	(Q) In the last 12 months were you slapped, hit or beaten by your mother-in-law?. (A) Never, sometimes, often	A positive response to one or both items coded as yes		Decrease
Perceptions of mother-in-law cruelty.	For married women who currently live with their mothers-in-law, six items ask about their relationship and the mother-in-law’s attitudes towards her.	(Q) My mother-in-law can frighten me (A) Strongly disagree; disagree; agree; strongly agree	Mean score: higher scores indicate more cruelty	0.84	Decrease

The secondary outcomes for the study reflect the multiple objectives of the intervention and fall into four categories: economic outcomes; mental health and wellbeing; gender attitudes, and power and violence outcomes.

Secondary economic outcomes are:Past four week household food insecurity;Financial shock resilience;Women’s past month earnings; andWomen’s total savings.

Secondary mental health and wellbeing outcomes are:Current life satisfaction; andPast four week suicidal ideation.

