### Baseline comparison

Despite the challenges of implementing research in a complex environment, where there was high demand for inclusion in the study and intervention, the baseline socio-demographic data shows comparability between study arms, showing randomization was effective (Table 2). There were no significant differences between study arms, either amongst all women (*n* = 1461), or amongst married women only (*n* = 935).

**Table 2 Tab2:** Socio-demographic information by study arm

	All women						Currently married women only					
	Total	Intervention		Control		*p*-value	Total	Intervention		Control		*p*-value
		mean	(95% CI)	mean	(95% CI)			mean	(95% CI)	mean	(95% CI)	
*Age*	1461	29.3	28.7–29.9	29.3	28.6–30.0	0.99	935	32.4	31.8–33.0	32.4	31.7–33.1	0.97
		n	(%)	n	(%)			n	(%)	n	(%)	
*Relationship Status*												
Currently married	935	481	64.4	454	63.6							
Previously married	98	48	6.4	50	7.0							
Never married	428	218	29.4	210	29.4	0.89						
*Education*												
None	1129	581	77.8	548	76.8		781	408	84.8	373	82.2	
Madrasa	92	52	7.0	40	5.6		47	25	5.2	22	4.9	
Primary schooling	147	74	10.1	73	10.2		75	36	7.5	39	8.6	
Secondary schooling	93	40	6.4	53	7.4	0.31	32	12	2.5	20	4.4	0.38
*Borrowing food or money in past month because of not having enough*												
No	437	215	28.9	222	31.1		281	141	29.4	140	30.9	
Yes	1021	530	71.1	491	68.9	0.34	651	338	70.6	313	69.1	0.63

The average age of the respondents was just under 30 (29.3 intervention, 29.3 control). In both arms, just under two-thirds were currently married, and just under 30 % had never been married. Education levels in the whole sample were low: three-quarters of women had never received any formal education (77.8% intervention, 76.8% control). Of the quarter who had received education, around 6% had been to a Madrasa, 10% had received some form of primary school education, and 6.4% (intervention) and 7.4% (control) had some level of secondary education. There were also high levels of poverty, with approximately 70 % of the sample reporting borrowing food or money in the past month because they did not have enough.

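### Emotional IPV is set in women married at endline but assessed as change from baseline, so women who first marry during follow-up are in the set with no change score

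*Protocol article*

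**What the plan says.** Two rules in Data management and analysis apply to emotional IPV.

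- The set: "The main analysis for outcomes of intimate partner violence will be conducted on a sub-set of the sample who are currently married at endline".
- The quantity: "For outcomes using scales, the difference in the scores between baseline and 12 months, and baseline and 24 months will be assessed". The model follows: "For each of the scales, a linear mixed model will be fitted with fixed terms for treatment arm". The article does not say whether the dependent variable of that model is the change or the score at each visit.

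Table 1 lists past-year emotional IPV as a secondary outcome in currently married women, scored as a mean of seven items about the husband. Physical and severe physical IPV carry the same population label but are yes/no outcomes.

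Eligibility criteria limits who can answer such items: "it is only feasible to ask IPV questions of currently married/previously married women". Table 2 gives the never-married row at baseline: "Never married 428 218 29.4 210 29.4 0.89", that is 428 women, 218 in the intervention arm and 210 in the control arm.

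**The concern.** The set is defined at endline, while the quantity needs a score at baseline. A woman with no husband before or at baseline has no baseline answer to items about a husband. If she marries during follow-up she enters the set, yet nothing can be subtracted from her later score. If she marries after the 12-month visit she has no 12-month score either.

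Physical IPV needs no baseline value, so the same woman is counted there. An analyst who follows the text literally therefore estimates emotional IPV in a narrower group than physical IPV, under one label. Readers would set the two results side by side as describing one population. Some precision is lost as well. If the choice of population is left open, it may be made after outcome data have been seen.

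**Working it through.** The article states no figure on this point. Its sample sizes (337 and 422 per arm) concern the two binary IPV outcomes and are not in question here.

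**Step 1: follow one woman through the rules.** She is never married at baseline, marries at month 15 and is interviewed at month 24.

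| Outcome | In the endline-married set? | Needs a baseline value? | Counted? |
|---|---|---|---|
| Physical IPV (binary) | Yes | No | Yes |
| Emotional IPV, as change from baseline | Yes | Yes, and none exists | No |
| Emotional IPV, as 24-month score | Yes | No | Yes |

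**Step 2: inputs.** From Implementation and Table 2: 1461 randomised, of whom 935 currently married, 98 previously married and 428 never married (428/1461 = 29.3%). Only the 428 are certain to lack a baseline score, because previously married women could have been asked IPV items.

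**Step 3: is marriage during follow-up plausible?** Table 2 gives a mean age of 29.3 overall and 32.4 in married women. If previously married women average a years (assumed), the never-married mean is (1461×29.3 − 935×32.4 − 98a)/428. This is 22.4 for a = 30 and 20.1 for a = 40. Some marriages within 24 months are plausible, but ages do not give a rate.

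**Step 4: size.** Let m be the share of the 428 who marry by endline (assumed). Assume also that all 935 stay married and that follow-up is equal in both groups. The share without a change score is 428m/(935 + 428m). If each such woman carried as much information as any other, dropping them would multiply the standard error by (1 − share)^−0.5.

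| m | Women affected (428m) | Share of the set | SE factor |
|---|---|---|---|
| 5% | 21.4 | 21.4/956.4 = 2.2% | 1.011 |
| 10% | 42.8 | 42.8/977.8 = 4.4% | 1.023 |
| 20% | 85.6 | 85.6/1020.6 = 8.4% | 1.045 |
| 30% | 128.4 | 128.4/1063.4 = 12.1% | 1.066 |

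The SE factors are upper limits on recoverable precision for each m, because a woman without a baseline score adds less information than one who has it. The share would be higher if some of the 935 were no longer married at endline, or if previously married women without a baseline score remarried.

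**The case against.** The strongest reply is that the article does not fix a change-score model. It compiles one dataset from three visits and fits a linear mixed model without naming the dependent variable. A mixed model on repeated scores can yield differences from baseline and keep women who have only follow-up scores. This stands as a possible reading. However, the sentence just before the model names the difference as what is assessed, and nothing in the text points to the other reading.

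A second reply is that handling of missing baselines is commonly left to the analysis plan. That is true, and the absence of such a rule is not the point. The point is that two stated rules cannot both be applied to the same woman.

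A third is that requiring a husband at baseline is a defensible population. It is, but it is not the one stated for IPV outcomes.

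A reader might go further and infer that husband cruelty, household decision making and mother-in-law cruelty have the same defect. The text does not support this. The endline-married set is stated only for IPV outcomes, and these scales carry no time point for being married. The gap reaches husband cruelty and decision making only if marriage is read at follow-up. For mother-in-law cruelty the items go to "For married women who currently live with their mothers-in-law, six items ask about their relationship and the mother-in-law’s attitudes towards her", so a difference needs co-residence at both visits. Redefining that set by co-residence at follow-up would condition on a living arrangement that arises after randomisation. That is a trade-off, and no change to it is proposed here.

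A reader might also infer bias between arms. Nothing in the documents shows it: never-married women are balanced at baseline (218 and 210), and no effect of the programme on marriage is reported.

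**Conclusion.** The point holds for emotional IPV. Under the stated set and the stated difference, women never married at baseline who marry by endline belong to the analysis but cannot contribute, while they do contribute to physical IPV.

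The effect is modest: about 2% to 12% of the endline-married set and at most about a 1% to 7% rise in standard errors. These ranges rest on an assumed 5% to 30% of the 428 marrying, all 935 staying married, and equal follow-up. No marriage rate is given, so the true figure could lie outside them.

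Only a secondary outcome is affected. Both physical IPV outcomes are binary, and depression is analysed in the whole sample. The change is still worth making, because the mismatch of populations arises from the plan's own wording and is cheap to remove.

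**What to change.** For emotional IPV, and for any other married-only scale that is analysed in women married at endline:

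- Make the 12- and 24-month score the outcome of the linear mixed model in place of the change score. A woman who marries after month 12 then contributes her 24-month score.
- Adjust for the baseline score and an indicator for having no baseline score. For never-married women that indicator reflects marital status fixed before randomisation.
- Use the same women for emotional IPV as for physical IPV.
- Show the result in women married at both baseline and endline as a sensitivity analysis.
- State, for each married-only scale, the visit at which being married is judged.

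The planned item weights are no obstacle. They come from baseline items and can be applied to any woman's follow-up items.

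The cost is analysis wording and model code, with no new data. There are two small downsides. The estimate is no longer a within-woman change, and recently married women have had less than a full year of exposure to past-year items. The second already applies to physical IPV in the stated set, and the sensitivity analysis shows how much it matters.
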